#### Early termination of this trial

This trial will be terminated early in any of the following situations:

(1) the trial needs to be terminated for efficacy or futility based on the results of interim analysis; (2) the trial will continue based on the results of interim analysis and the target number of participants is modified or the target number of participants is reached prior to the scheduled conclusion of enrollment; (3) the Central Ethics Review Committee recommends that the trial be terminated due to serious adverse events; or (4) the Central Ethics Review Committee deems that the trial cannot be completed due to limited enrollment.

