#### Items analyzed and analytical methods

The participant characteristics in both groups will be described statistically. Mean values for weight, abdominal circumference, changes in marker levels for glucose and lipid metabolism, along with changes in cardiovascular biomarkers from enrollment until 9 months after enrollment, will be compared between the two groups. The distribution of individual indices at baseline and at 9 months after enrollment will be determined for the two groups, and a *t* test or a Wilcoxon rank-sum test will be performed. In addition, Fisher’s exact test will compare the percentage of individuals who quit smoking for a prolonged period in the two groups. The level of significance will be 0.05 or less. A two-tailed alpha of 5% and a two-sided 95% confidence interval will be used. The statistical analysis will be performed by a statistician. The primary endpoint will be assessed statistically to facilitate an interim analysis. Nutritional guidance will be deemed effective or ineffective in the final analysis using the statistic *Z*_prop_ = 1.567. An interim analysis will be performed after the 125 participants (an intermediate number of individuals out of the total enrollment) complete follow-up. This interim analysis will determine whether to terminate this trial for efficacy or futility. Trial termination for efficacy will be based on *Z*_prop_ > 2.538, whereas trial termination for futility will be based on *Z*_prop_ < 0.698.

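### Item (2) of the early-termination list allows the target number to change after the comparative interim with no rule, while the single final threshold of 1.567 assumes a pre-planned second stage; this can inflate the type I error

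*Protocol article*

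**What the plan says.** In the Protocol article, Items analyzed and analytical methods sets the interim: "An interim analysis will be performed after the 125 participants (an intermediate number of individuals out of the total enrollment) complete follow-up". Its stated purpose is a stop-or-continue decision, made in either direction against two bounds: "Trial termination for efficacy will be based on *Z*_prop_ > 2.538, whereas trial termination for futility will be based on *Z*_prop_ < 0.698". The final rule is one number: "Nutritional guidance will be deemed effective or ineffective in the final analysis using the statistic *Z*_prop_ = 1.567". That section does not mention changing the sample size, and it does not define the statistic.

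The section Early termination of this trial opens with "This trial will be terminated early in any of the following situations". Its item (2) covers two cases. In the first, "the trial will continue based on the results of interim analysis and the target number of participants is modified". In the second, "the target number of participants is reached prior to the scheduled conclusion of enrollment". It gives no rule, direction or limit for the modification, and no change to the final test.

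**The concern.** The two sections do not fit together. One gives the interim a stop-or-continue role with fixed bounds. The other adds a third possible outcome, continuation with a different target, chosen by people who know the interim comparison. Stopping on a between-group Z requires a comparative look, so this is not a blinded re-estimation of the SD.

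A group-sequential final threshold is calculated for a second stage whose size is set in advance. If that size can be chosen after the interim Z is known, and the ordinary pooled statistic is still compared with 1.567, a choice that favours rejection raises the false-positive rate of the primary comparison.

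Item (2) also contradicts its own heading, because a trial that continues is not a trial terminated early.

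**Working it through.** **Inputs.** The interim bounds 2.538 and 0.698 and the final value 1.567 come from Items analyzed and analytical methods. The interim is at 125 of 250 participants, so the planned stages are equal and the information fraction is t = 125/250 = 0.5. I assume that the statistic is the ordinary pooled Z.

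**The plan's own error rate.** Under the null, one-sided:

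- P(Z1 > 2.538) = 0.0056
- P(0.698 < Z1 < 2.538 and Z2 > 1.567) = 0.0444
- Sum = 0.0500

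The bounds therefore spend 5.0% one-sided with binding futility, about 10% if doubled. The article says "A two-tailed alpha of 5% and a two-sided 95% confidence interval will be used", which these bounds do not reproduce. That is a separate point; here 5.0% one-sided is the reference. If the futility bound is not followed, the reference is 0.0601.

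The value 2.538 is also what O'Brien-Fleming-type spending gives for a one-sided 5% at t = 0.5: 2 × [1 − Φ(1.96/√0.5)] = 0.0056. The three numbers thus fit an ordinary group-sequential design on a pooled Z.

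**Effect of resizing.** Let r be the actual second-stage size divided by the first-stage size; the plan has r = 1. Given Z1 = z, the pooled Z crosses 1.567 under the null with probability

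1 − Φ( (1.567·√(1 + r) − z) / √r ).

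This depends on r. At z = 1.8 it is 0.339 for r = 1 and 0.433 for r = 0.5. At z = 0.8 it is 0.078 for r = 1 and 0.089 for r = 3. Cutting the second stage after a strong interim, or enlarging it after a weak one, helps rejection.

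The worst case takes the most favourable allowed r at each z, integrates over the continuation region against the null density, and adds 0.0056:

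| Allowed r | Futility binding | Futility not followed |
|---|---|---|
| 1 (as planned) | 0.0500 | 0.0601 |
| 1 to 2 | 0.0506 | 0.0680 |
| 1 to 3 | 0.0507 | 0.0723 |
| 0.5 to 1 | 0.0570 | 0.0671 |
| 0.5 to 2 | 0.0577 | 0.0750 |
| 0.5 to 3 | 0.0577 | 0.0793 |

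**Not every rule inflates.** Doubling the second stage only when Z1 ≥ 1.108 (= 1.567·√0.5, conditional power of at least 50% under the current trend) gives 0.0432 with binding futility.

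**Check of the remedy.** In 4 million simulated null trials, the second stage was tripled when Z1 < 1.108 and halved otherwise, with binding futility. The pooled Z against 1.567 rejected in 0.0574. The statistic (Z1 + Z2*)/√2, where Z2* is computed from second-stage data only, rejected in 0.0500 with the same three cutoffs.

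**The case against.** The strongest case is that the text shows no inflation. It gives no direction for the change. The usual interim resizing is an increase, and with binding futility increases alone add at most 0.07 percentage points. That stands, and it is why the point says the error can rise.

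A large cut is also limited in practice. Assume even accrual of 250 over the 3-year enrollment period, 6.94 per month. Without dropout, the 125th completer is reached at month 18 + 9 = 27, when about 188 are enrolled, so r cannot fall below about 63/125 = 0.5. With 25% dropout, 125/0.75 = 167 must enroll, which takes 24 months. At month 33 about 229 are enrolled, and the second stage could shrink only by about a quarter. This also stands. A reader might infer much larger error rates by letting the second stage shrink to almost nothing; this timing does not support them.

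The statistic is undefined, and the full protocol or SAP may specify a pre-weighted combination, which would remove the problem. That is possible. However, the printed bounds fit an ordinary group-sequential design, nothing in the article points to a combination test, and the article itself prints both the fixed threshold and the clause that can invalidate it.

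Finally, a reader might infer from item (2) that follow-up is cut off once the target is reached. The text does not support that: the clause refers to the scheduled end of enrollment, and the assessments are fixed at 9 months after enrollment elsewhere in the article. This part is a wording fault with no effect on the error rate.

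**Conclusion.** The point holds in a limited form: item (2) permits an unconstrained change of target after a comparative interim, and the article keeps one final threshold that is valid only for a pre-planned second stage.

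Against 5.0% one-sided, the worst case is about 5.1% for increases only and 5.7-5.8% if the second stage may be halved, both with binding futility. If the futility bound is not followed, the reference is already 6.0%, and the worst case is about 7% for increases up to three times and about 8% if halving is also allowed.

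These figures assume a pooled Z, equal planned stages and a choice of size made to favour rejection. They are upper limits for each range, not predictions. The documents do not show that the trial will inflate its error, because some resizing rules lower it. The change is still worth making, because no rule confines the choice and the remedy is cheap.

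**What to change.** Either of two amendments, made before the interim, is enough:

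1. Delete the target-modification words from item (2), so that the interim has only the efficacy and futility role described in the analysis section. The cost is the loss of freedom to resize.
2. Keep the option, and state that after any interim-driven change the final test is the inverse-normal combination of the two stage-wise Z statistics at pre-fixed equal weights, (Z1 + Z2*)/√2, with the same three cutoffs. The cost is slightly inefficient weighting when the stages turn out unequal.

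Separately, reword the rest of item (2) and move it out from under the early-termination heading: reaching the target closes enrollment, and all enrolled participants complete the 9-month assessment. This costs one sentence.

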## Discussion

Smokers are typically known to gain weight after SC [5]. Specific causes of weight gain after SC are not known; however, studies have suggested various factors, such as increased appetite, restoration of taste and smell, increased dietary intake as a result of oral cravings, improved gastric mucosal microcirculation, and a lower resting basal metabolic rate [23]. Weight gain is noted approximately 3 years after quitting smoking [24] worsening glucose tolerance [23, 25, 26]. The fear of gaining weight leads individuals to resume smoking [27, 28]. A study on women who resumed smoking due to a fear of gaining weight has reported that SC treatment with nicotine gum and a very-low-calorie diet helped to inhibit weight gain and increased the percentage of women who successfully quit smoking [13]. Drug therapy, such as nicotine replacement therapy, inhibits weight gain during SC treatment [23], leading to an increased percentage of individuals who successfully quit smoking [29]. Nonetheless, increased appetite as a result of a serotonin deficiency has been noted upon the conclusion of drug therapy [30]. This will be the first large-scale, prospective, randomized controlled trial to examine the effectiveness of nutritional guidance for individuals who are likely to gain weight after SC upon the conclusion of treatment.

The primary endpoint in this trial is the adiponectin level. Adiponectin has anti-inflammatory action, action to protect blood vessels, and action to inhibit atherosclerosis. Adiponectin levels in the blood decrease as a result of obesity, particularly because of increased visceral fat [31]. Serum adiponectin levels are also known to decrease because of smoking [31], which might be closely related to the occurrence of cardiovascular events [32, 33]. A study has reported that adiponectin levels predict future cardiovascular disease [34–36]. If weight gain is inhibited among individuals who quit smoking for a prolonged period, then their cardiovascular risk might decrease. In fact, our group has previously reported that patients who quit smoking for a prolonged period and whose weight gain was inhibited showed improved levels of cardiovascular biomarkers, such as increased serum adiponectin levels. Given that adiponectin is a marker that reflects both the effects of quitting smoking and inhibition of weight gain, adiponectin level was chosen as the primary endpoint for this trial.

The current trial will determine the effectiveness with which nutritional guidance prevents obesity after SC and will compare the effects of nutritional guidance on cardiovascular, glucose, and lipid metabolism biomarkers. This trial will involve individuals who successfully quit smoking with the help of a SC clinic and gained weight. If the advantages of quitting smoking are enhanced further by preventing obesity after quitting smoking, then cardiovascular disease development, and subsequent medical expenditures, should be sharply reduced. An increased appetite after quitting smoking is a sign that nicotine withdrawal is abating, but the undeniable reality is that forcefully curtailing appetite through severe dietary restrictions can prompt individuals to resume smoking. Nutritional guidance can inhibit weight gain, but it does more harm than good if the individual resumes smoking. Thus, the current trial will also examine the effects of nutritional guidance on the percentage of individuals who quit smoking for a prolonged period. Treatment in this trial is completely covered by National Health Insurance. However, the participants receiving nutritional guidance will be put at a disadvantage because of the increased number of visits and the fee for nutritional guidance. Nonetheless, a study has reported that nutritional guidance after quitting smoking helps inhibit obesity after SC and increases the percentage of individuals who quit smoking for a prolonged period [12]. Nutritional guidance could, potentially, reduce an individual’s cardiovascular risk. The results of this trial should help to improve the quality of SC treatment in the future.

### Trial status

At the time of manuscript submission, recruitment for this study is ongoing.

## Abbreviations

AT-LDL: α1-antitrypsin low-density lipoprotein complex
BMI: Body Mass Index
CO: Carbon monoxide
EDC: Electronic Data Capture
FTND: Fagerström Test for Nicotine Dependence
hsCRP: High-sensitivity C-reactive protein
LOX-1: Leptin-like oxidized low-density lipoprotein receptor-1
SAA-LDL: Serum amyloid A-LDL complex
SC: Smoking cessation
SD: Standard deviation
SDS: Self-rating Depression Scale
